## 2. Materials and Methods

### 2.1. Study Design

This is a cross-sectional, vignette-based experiment with a four-level within-subjects (repeated-measures) design. Vignette experiments combine the internal validity of experimental manipulation with survey feasibility and are an established method for isolating drivers of health-related judgments [61]; their design and analysis follow current methodological guidance for vignette data [62]. Each participant reads and evaluates all four scenarios of AI implementation (A–D), presented in a counterbalanced sequence. The within-subjects structure makes each respondent their own control, eliminating inter-individual variability from between-scenario comparisons and substantially increasing statistical power relative to a between-subjects design of the same size [63]. The presentation sequence is counterbalanced. The survey platform allocates participants at random, in equal proportions and independently of any participant characteristic, to one of the four sequences of a Williams (balanced Latin-square) design: A → B → C → D, B → D → A → C, C → A → D → B, and D → C → B → A. In this square, every scenario occupies every serial position exactly once, and every ordered pair of scenarios occurs exactly once, so that autonomy level is orthogonal both to serial position and to first-order carry-over, and an additive model containing a four-level autonomy effect and a four-level serial-position effect is fully identified. The theoretically motivated ascending sequence and its exact mirror image are retained as two of the four arms. A fixed ascending presentation would have mirrored the progressive continuum under investigation and given every participant an identical evaluation context, but it would have left order, carry-over, and fatigue effects inseparable from the autonomy gradient; because H1–H3 concern precisely that gradient, internal validity was given priority over uniformity of context. Counterbalancing also makes the embedded manipulation check diagnostic rather than merely descriptive: perceived AI control should track the described autonomy level within every sequence, whereas an anchoring or fatigue artifact would instead track serial position—a distinction that a monotonic manipulation-check profile obtained under a fixed order cannot draw. Presentation sequence is therefore retained as a between-subjects factor in all primary models, a second manipulation check (perceived technical sophistication) separates autonomy from technical complexity, and a per-scenario difficulty item indexes fatigue (Section 2.6, Section 2.7, Section 2.8, and Section 2.9.1). The study involves no medical, pharmacological, or surgical intervention. Reporting of the completed study will follow current recommendations for effect-size-based reporting [64] and, for the web-survey component, the CHERRIES checklist as operationalized in recent methodological guidance [65]. Publication of the protocol in advance of data collection is intended to reduce publication bias and analytic flexibility [66,67].

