
### 2.9. Statistical Analysis

#### 2.9.1. Primary Analyses

Each composite score (acceptability, trust, perceived risk) will be analyzed by a mixed repeated-measures ANOVA, with autonomy level (four scenarios) as the within-subjects factor and presentation sequence (four Williams sequences) as the between-subjects factor. The Greenhouse–Geisser correction will be applied when Mauchly’s test indicates a sphericity violation (Huynh–Feldt for ε between 0.75 and 1), and the multivariate approach (Pillai’s criterion) will be reported in parallel as a sphericity-robust check. H1 and H2 will be tested with within-subjects trend contrasts across the autonomy gradient. Because acceptance need not fall in a straight line, the complete set of orthogonal polynomial contrasts—linear, quadratic, and cubic—is pre-specified, and each is reported together with the proportion of the omnibus effect it accounts for. A purely linear profile leaves the quadratic and cubic components negligible, whereas a step between two adjacent levels appears as a large linear component accompanied by a substantial quadratic or cubic one. Because every monotone step is linear-dominant, the polynomial decomposition establishes departure from a straight line but cannot by itself locate the break; the break is identified only from the Holm-corrected adjacent-pair contrasts (A–B, B–C, C–D). A quadratic-dominant profile with a small linear component would instead indicate a non-monotone pattern, which the hypotheses do not predict and which would be reported as such. A non-monotonic or threshold pattern will be reported as such rather than summarized by the linear trend alone. Post hoc comparisons use dependent-samples *t*-tests for the six scenario pairs with Holm’s sequential correction, applied within each hypothesis-defined family of tests in line with current guidance on multiplicity control [74]. Effect sizes will be reported as partial η^2^ for omnibus tests and Cohen’s dz for pairwise comparisons, with 95% confidence intervals, following effect-size-centered reporting recommendations [64]. Assumption checks include graphical inspection of difference-score distributions; as a distributional robustness analysis, the Friedman test with Holm-corrected Wilcoxon signed-rank pairwise comparisons will be reported alongside each primary test—supplemented by ordinal (cumulative-link) models as sensitivity analyses for the Likert-based outcomes [71]—and the concordance of parametric and nonparametric conclusions stated explicitly. Order dependence is tested directly as the scenario × sequence interaction; a non-significant interaction, together with equivalence of the four sequence-specific profiles, supports pooling across sequences. Independently of that test, the autonomy effect is re-estimated from a linear mixed model with random intercepts per participant and additive fixed effects of autonomy level and serial position (1–4). The Williams square renders this model identified, so the estimate is adjusted for arbitrary—not merely linear—serial-position and fatigue effects, while first-order carry-over is balanced by the design rather than modeled; position-adjusted and unadjusted estimates are reported side by side, and any material divergence between them is treated as evidence of an order artifact and interpreted accordingly. Perceived difficulty (DIF1) and perceived technical sophistication (MAN2) are each added as time-varying covariates in further sensitivity models, addressing fatigue and the possibility that responses track the apparent complexity of the system rather than its autonomy. Finally, between-person heterogeneity in response profiles is examined by adding a random slope for the linear autonomy contrast and testing the improvement in fit by a likelihood-ratio test; a substantial random-slope variance indicates that an average trajectory conceals distinct response patterns and licenses the exploratory typology described in Section 2.9.2. Because a non-significant test is not evidence of absence, a smallest effect size of interest of *dz* = 0.20—the value detectable at the Bonferroni bound for the six pairwise contrasts at *N* = 300—is fixed in advance, and equivalence testing by two one-sided tests against that bound is reported alongside every null pairwise result, so that any claim that two adjacent scenarios do not differ rests on an equivalence test rather than on the absence of significance.

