## 3. Expected Results

Based on the algorithm-aversion and trust studies [19,37,38], we expect acceptability and trust to decline—and perceived risk to rise—across the autonomy gradient from Scenario A to Scenario D, with the largest drop anticipated at the transition to autonomous planning (Scenario D), where the surgeon’s corrective role is described as residual. Whether that decline is a gradient or a step is an open question that the design is equipped to address: a step would show as a substantial quadratic or cubic component alongside the linear one, and its location would be identified by the adjacent-pair contrasts, which we expect to place the largest single drop at C–D. Nor do we assume the pattern is homogeneous across participants; a substantial random-slope variance would itself be informative, indicating that an average trajectory conceals distinct groups of respondents rather than describing a shared response. The expectation of decline is, in any case, consistent with survey evidence that public comfort is conditional on physician supervision [24,25,31]. For responsibility attribution, we expect the surgeon to be assigned the dominant share in low-autonomy scenarios [41], with a progressive migration toward the AI developer—and possibly a diffusion of responsibility across actors, indexed by falling Herfindahl concentration—as autonomy increases [44,45]. We expect the manipulation check (perceived AI control) to order the scenarios from A to D within each of the four presentation sequences, validating the experimental gradient independently of serial position, and we expect no scenario × sequence interaction. Should one nevertheless appear, the position-adjusted mixed-model estimate becomes the primary basis for interpreting H1–H3, and the magnitude of the order effect will itself be reported as a finding about the stability of vignette-based autonomy judgments. Given the design’s sensitivity (power of 0.99 against small within-subjects effects at ρ = 0.50, and 0.95 at ρ = 0.30, for the target sample), a null result for a primary hypothesis would place a tight upper bound on the size of any autonomy effect rather than leaving the question open; the pre-specified equivalence tests of Section 2.9.1 make that bound explicit rather than infer absence from non-significance [70]. The moderation hypothesis (H4) is powered only for medium-small interactions and will be interpreted with corresponding caution. Results will inform the ordering of public concerns along the assistance-to-autonomy continuum and identify which implementation configurations are publicly acceptable entry points for surgical AI in Romania.

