Several limitations are accepted by design and will be declared in the results article. First, the sample is a self-selected online convenience sample: results describe Romanian adults active in digital environments—likely younger and more educated than the general population—and do not support national generalization; the sample structure will be reported against National Institute of Statistics reference data. Second, the vignettes are hypothetical, and the distance between a vignette judgment and a decision taken in a consulting room is not merely one of degree. Participants evaluate a scenario in which they are not injured, not in pain, not facing a scheduled operation, and not choosing between real surgeons. They bear no consequences for the judgment they record, receive no counseling, and cannot ask questions. Above all, they are not exposed to the most influential element of real surgical decision-making: a conversation with the clinician who would operate, whose endorsement and explanation are known to shift acceptance of AI-supported care substantially [27,28]. Stated acceptability under these conditions is best read as a measure of prior disposition toward a described scenario rather than as a prediction of consent behavior. The ordering of the scenarios is likely to be more robust than the absolute levels, which could be lower than those a counseled patient would report or higher if hypothetical risk is discounted. This is a standard limitation of vignette methodology [61,62], and the remedies lie outside the present design: replication among patients actually scheduled for facial reconstructive surgery, and ultimately observation of consent decisions where such systems are in use. Third, presentation sequence is counterbalanced but not thereby rendered irrelevant. The Williams square balances serial position and first-order carry-over, so that the autonomy effect is estimable free of both, but no four-sequence design balances higher-order carry-over—a participant’s evaluation of the third scenario being shaped jointly by the first two—and contrast effects that depend on which scenario was seen immediately before therefore remain possible. The scenario × sequence interaction, the position-adjusted model, and the difficulty covariate bound the magnitude of what remains; they do not remove it, and a large residual would warrant a between-subjects replication in which each participant evaluates a single scenario. Fourth, demand and contrast effects are inherent to within-subjects designs: seeing all scenarios, participants may infer the study objective and exaggerate differentiation between scenarios; comparisons remain internally valid, but absolute difference magnitudes warrant caution. Fifth, all measures share a common method and a single measurement occasion, in a rapidly evolving attitude domain [38]. Sixth, the survey platform does not record completion time, so quality control relies on embedded checks rather than temporal filters [69]. Seventh, the demographic and familiarity subgroups formed within a convenience sample of 300 will differ substantially in size, and several will be small; the minimum-cell rule of Section 2.9.2, and the requirement that subgroup differences be inferred only from formal interaction terms, are intended to forestall the familiar error of asserting a difference from a significant effect in the larger subgroup together with a non-significant one in the smaller. None of these limitations is unusual for online vignette experiments, and declaring them in advance is intended to keep the eventual findings interpretable at their proper scope.

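### Under the planned balance the position-adjusted and unadjusted scenario estimates coincide, so the divergence rule and the fallback for H1–H3 add almost nothing, and first-order carry-over is left in both

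*Protocol article*

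**What the plan says.** Section 2.1 allocates participants "in equal proportions and independently of any participant characteristic, to one of the four sequences of a Williams (balanced Latin-square) design". It notes that "every scenario occupies every serial position exactly once" and concludes that "autonomy level is orthogonal both to serial position and to first-order carry-over". Section 2.9.2 (xiii) restricts the analysis to participants with all four scenario blocks.

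Section 2.9.1 tests order dependence by the scenario × sequence interaction. It then re-estimates the autonomy effect from a model with "random intercepts per participant and additive fixed effects of autonomy level and serial position"; first-order carry-over is not modelled, on the ground that the design balances it. The reading rule is that "position-adjusted and unadjusted estimates are reported side by side, and any material divergence between them is treated as evidence of an order artifact". Table 5 lists adjusted against unadjusted scenario means as an order output.

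Section 3 says that if an interaction appears, "the position-adjusted mixed-model estimate becomes the primary basis for interpreting H1–H3". The limitations in Section 4 describe the autonomy effect as estimable free of both serial position and first-order carry-over. They concede higher-order carry-over and add that "a large residual would warrant a between-subjects replication in which each participant evaluates a single scenario".

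**The concern.** The orthogonality of scenario and position that Section 2.1 relies on is the very property that stops a position adjustment from moving a scenario contrast. A comparison that cannot differ tells the reader nothing about order, and a fallback that returns the same numbers protects nothing.

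Two further problems follow. The fallback is triggered by an interaction that contains pure position effects, which do not bias the contrasts. Carry-over, which does bias them, appears in neither estimate as a modelled term. At stake is the claim, named in Section 4 as a principal contribution, that the autonomy gradient is separated from both position and first-order carry-over.

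**Working it through.** **Inputs from the protocol.** Sequences ABCD, BDAC, CADB, DCBA; equal allocation (75 each at N = 300); complete cases; ρ = 0.50; α = 0.05. **Assumed, because the protocol gives none:** the sizes of position and carry-over effects, unequal counts, and any decay of correlation.

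**1. The plan's own figures.** With noncentrality λ = N·4·f²/(1−ρ) and error df 3(N − number of groups): N = 138 for f = 0.10; at N = 300 the minimum detectable f is 0.0675 (autonomy) and 0.0811 (interaction), and power at f = 0.10 for the interaction is 0.952. These match the stated 138, 0.07, 0.08 and 0.95.

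**2. Equal counts.** Write a cell as τ(scenario) + π(position). Each scenario stands once in each position, so its raw mean is τ + (π1+π2+π3+π4)/4. The second part is common to all scenarios and cancels from every contrast. Fits on 75 per sequence with position effects 0, −0.3, −0.6, −0.9 agree: the largest adjusted-minus-unadjusted difference is 4e-14. In that data set the model's own position term gave a Wald χ²(3) of about 136, and the standard error of D−A fell from 0.090 to 0.084.

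**3. Unequal counts, 85/70/75/70, same drift.** D stands in positions 4, 2, 3, 1 and A in 1, 3, 2, 4 across the four sequences.
- D is shifted by (85×(−0.9) + 70×(−0.3) + 75×(−0.6) + 70×0)/300 = −142.5/300 = −0.475.
- A is shifted by (85×0 + 70×(−0.6) + 75×(−0.3) + 70×(−0.9))/300 = −127.5/300 = −0.425.
- Raw D−A moves by −0.05 (−1.550 against a true −1.500); the adjusted model returns −1.500.

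Under simple random allocation of 300 with this drift, the largest contrast difference averages 0.045 (95th percentile 0.088).

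**4. What the interaction contains.** On the 16 sequence-by-scenario cells, scenario plus sequence has rank 7, adding position gives 10, and adding first-order carry-over gives 13. The 9 interaction df are therefore position 3, carry-over 3, residual 3. A drift of 0.10 SD per position has centred effects −0.15, −0.05, 0.05, 0.15, with sum of squares 0.05. Then λ = 300×0.05/(1−0.50) = 30, and power on (9, 888) df is 0.986. An effect that biases no scenario contrast would almost always trigger the fallback.

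**5. Carry-over.** Let λ_k be the effect on the next rating of having just read scenario k, and Λ the sum of the four. No scenario follows itself, so scenario j receives (Λ − λ_j)/4 on average. The bias of a contrast j−k is −(λ_j − λ_k)/4. With assumed effects of 0, 0.1, 0.2, 0.5 after A, B, C, D, the bias in D−A is −0.5/4 = −0.125. The unadjusted and position-adjusted fits both give −1.625; adding a first-order carry-over term gives −1.500. The variance of a scenario contrast then rises from 0.50 to 0.55 (in units of within-person residual variance over the number per sequence), a ratio of 1.10, so the standard error rises by √1.10 − 1 ≈ 5%. Scenario and carry-over are close to orthogonal but not orthogonal.

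**6. Standard errors of the fallback.** Random intercepts alone imply equal correlations. Suppose they decay as r, r², r³ with scenario distance. At r = 0.5 the mean correlation is (3×0.5 + 2×0.25 + 0.125)/6 = 0.354, so the model uses residual variance 0.646. The true variance of the normalised linear contrast is 0.9875, a ratio of 1.53. The nominal 5% test then rejects at |z| > 1.96/√1.53 = 1.585, a type I error of 0.11. At r = 0.7 it is 0.14. For adjacent pairs it is 0.03 and 0.02.

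**The case against.** A reader might infer that the additive model can neither detect nor correct anything. The documents do not support that. Section 2.5 names its 3-df serial-position main effect as an order test, and step 2 shows that the term works. Exact balance after exclusions is not promised: Section 2.7 only monitors it, and Section 2.9.2 anticipates differential drop-out. With unequal counts the model does remove a position shift from raw pooled means, and systematic divergence then does reflect an order effect. That stands, but the size of the divergence depends on the imbalance as well as the drift, so it does not measure the order effect.

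A reader might also infer that agreement between the estimates will be presented as proof of no artifact. No passage says so. The rule runs one way, and pooling rests on the interaction together with equivalence of the sequence profiles. The direct order test is untouched, and Section 4 says the order analyses bound what remains without removing it.

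On standard errors, Section 2.9.1 also plans a random slope for the linear autonomy contrast. In a small simulation (150 runs per setting, so approximate), type I error for the trend fell from 0.09 and 0.14 to 0.03 and 0.07 with that slope. The slope is planned as a heterogeneity analysis and not as part of the fallback, so this is partial relief. The decay pattern itself is an assumption.

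**Conclusion.** The point holds for the divergence rule and for the fallback's point estimates. Under equal counts and complete cases the two sets of scenario estimates are identical whatever the position effect; under modest imbalance they differ by about 0.05 points for a drift of 0.3 per position. First-order carry-over biases both by minus one quarter of the carry-over difference, which contradicts the statements in Sections 2.1 and 4 that autonomy is orthogonal to it or estimable free of it. The algebra rests only on the stated design; the sizes rest on the assumed drift, carry-over, counts and correlations.

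The primary ANOVA, the sample size, the serial-position term and the scenario × sequence interaction stand. This is a should-fix correction to rules that do not do what the plan says of them, not a flaw that invalidates the trial.

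**What to change.** 1. Delete the divergence criterion and judge position effects by the 3-df serial-position term. The side-by-side means may stay as description.
2. Partition the 9-df interaction into position, first-order carry-over and residual (3 df each), and treat only the last two as threats to H1–H3.
3. Base the fallback in Section 3 on a model that adds a first-order carry-over term, with an unstructured within-person covariance or robust standard errors in place of random intercepts only. Correct the wording in Sections 2.1 and 4 on orthogonality to carry-over.
4. Optionally report a comparison restricted to the scenario each participant read first. About 75 randomly allocated participants per scenario already form a between-subjects comparison of the kind Section 4 defers to a replication. Its minimum detectable f is about 0.19 at power 0.80, so it is a low-precision check and not a primary test.

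The cost is analysis wording and code, with no new data, and pre-registration has not yet taken place. The carry-over-adjusted intervals are somewhat wider, by about 5% from step 5 before any change in the covariance model.
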